**Methods:**

This study consists of two phases: (1) preliminary data collection and machine learning for well-being prediction; (2) intervention and evaluation of iCBTS for SWSD. Shift workers in the intensive care unit at Mie University Hospital will wear a wearable sensor that collects biometric data and answer daily questionnaires regarding their well-being. They will subsequently be provided with an iCBTS app for 4 weeks. Sleep and well-being measurements between baseline and the intervention period will be compared.

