## Methods

### Study Overview

This is a prospective interventional pilot study consisting of two phases: (1) preliminary data collection and the development of machine-learning models for well-being prediction, and (2) intervention and evaluation of iCBTS for SWSD. The study will include shift workers (physicians and nurses) working at a university hospital ICU. Participants will be asked to wear a wrist-worn biometric tracker 24 hours a day and answer daily questionnaires about their well-being. After phase 1, sleep and well-being data will be used to build an algorithm for well-being prediction. Phase 2 begins with the baseline period (1 week; data collection only), followed by 4 weeks of the intervention period (data collection+intervention) (see details of the two periods in the following Measurements and Intervention subsections). We will compare sleep duration, well-being, and other variables during the baseline and intervention periods in all participants. The primary outcome of this study will be mean sleep duration at the last week of the intervention.

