In this study, well-being prediction will be based on these five self-reported labels on a scale of 0 to 100, which are collected twice daily (8 AM and 8 PM). To predict well-being scores, we developed a job-based multitask and multilabel convolutional neural network–based well-being prediction model using pilot data from 14 participants with a total of 241 days of data collection [14]. Twenty-three daily features were extracted from the wearable sensor and daily surveys, including biobehavioral features such as sleep duration, sleep variability, the number of steps, and average and variability of heart rate for the previous 1-7 days; work-related features such as shift schedule and working hours; and daily habits such as alcohol and caffeine intake. The model extracted high-level features using convolutional kernels and predicted five well-being scores simultaneously for physicians and nurses. The prediction performance of the proposed model was compared with that of control models, including job role–based multitask only and multilabel only (doctors only, nurses only, and all participants), and baseline models such as support vector machine and random forest. The proposed model achieved the best performance in almost all of the evaluations performed. In particular, the happiness score, which is considered to be representative of well-being, is illustrated by a graphic that resembles a weather forecast: cloudy for scores 0-50, cloudy and partly sunny for scores 60-80, and sunny for scores 90-100 (Figure 2). The well-being prediction result is updated every morning on the app screen based on the data collected up to the previous evening.

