### Sample Size and Power Calculation

The results of the study performed during phase 1 showed that the mean sleep duration among 16 shift workers was 334.68 (SD 135.1) minutes. The mean sleep duration in the baseline period of phase 2 is assumed to be statistically similar to that assessed in phase 1, as these phases are performed under similar conditions. Based on the pilot study data with a small sample, mean sleep duration at week 4 of the intervention was assumed to be 30 minutes longer, with no change in the SD. Assuming a two-sided level of significance of 5%, power of 80%, and correlation coefficient of 0.8, using the SAS system (SAS Institute Inc, Cary, NC), the number of participants needed for a significant difference to be found in the paired *t* test was calculated to be 66. We set the required number of participants at 70 because the dropout rate of the study was assumed to be about 5% of the enrolled individuals. Dropout rates of face-to-face CBTI in randomized controlled trials are reported to range from 0% to 8% [15]. According to prior studies, the mean attrition rate of internet-based psychological intervention programs performed in the workplace is 23%, with a range of 3% to 54% [16]. Dropout rates of internet-based sessions tend to be higher than those of face-to-face sessions. However, we estimate that a low dropout rate can be achieved due to the high frequency of feedback from sleep physicians. In addition, a prior study performed in the same ICU targeting health care workers using wearable sensors showed a low dropout rate of 0% [17]. At Mie University Hospital where this study is performed, approximately 75 medical staff members are working in the ICU at any given time, and about 95% of them can be expected to provide consent and participate in the study.

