### Outcome and Statistical Analysis

The primary outcome of this study is mean sleep duration on week 4 of the intervention. The means and SDs of sleep duration will be calculated at both the baseline data collection period and at week 4 of the intervention period. For the primary endpoint, a two-sided paired *t* test will be performed and assessed at the 5% significance level. In addition, the mean and SD of the changes in sleep duration will be calculated based on the difference between the mean sleep duration of the baseline period and week 4 of the intervention period.

The secondary outcomes of this study are as follows: activity (calories burned, steps taken), subjective well-being, reaction time, and quality and quantity of sleep. Median and quartile values for week 1, week 4, and for the rate of change will be calculated, and the Wilcoxon signed-rank test will be performed at the 5% significance level on both sides. In addition, we will perform a regression analysis of the time-series data (autoregressive model). This analysis will include all data collected during the study period as opposed to other analyses, which will use only data collected at the first and last weeks of the study. The median and quartiles will be calculated for the PSQI, JESS, STAI, and GHQ scores at both pretest and posttest, and the Wilcoxon signed-rank test will be performed at the 5% significance level on both sides. Using the cases in phase 1 as the control group and the cases in phase 2 as the intervention group, the means and SDs of the change in sleep duration will be calculated, and the Student *t* test will be performed at a significance level of 5% on both sides. Additionally, descriptive analysis will be performed to summarize the baseline characteristics of the participants in both groups.

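### The unpaired Student t test of phase 2 against phase 1 probably counts some staff in both groups and compares changes over different lengths of time

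*Protocol article*

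**What the plan says.** Under Outcome and Statistical Analysis, the last inferential comparison sets the two phases against each other: "Using the cases in phase 1 as the control group and the cases in phase 2 as the intervention group". What it compares is each group's change in sleep duration, by a Student t test at the two-sided 5% level. The same section defines change once, for the primary outcome, as "the difference between the mean sleep duration of the baseline period and week 4 of the intervention period". It also says that analyses other than the autoregressive model use the first and last weeks only.

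The Study Overview gives that timetable to phase 2 alone: "Phase 2 begins with the baseline period (1 week; data collection only), followed by 4 weeks of the intervention period". Phase 1 is described as data gathering for the prediction model. Its length is not given, and only one overall mean and SD are reported for it (334.68 and 135.1 minutes, 16 people). The Intervention section says the prediction model was built "using pilot data from 14 participants with a total of 241 days of data collection".

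Under Sample Size and Power Calculation, the target is 70 participants, 66 after dropout, from a unit where "approximately 75 medical staff members are working in the ICU at any given time". The eligibility criteria do not mention earlier participation in phase 1.

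**The concern.** A two-sample Student t test needs two separate sets of people, and it needs the outcome to mean the same thing in each set. The article's own figures put both conditions in doubt. Phase 2 intends to enrol almost the whole unit from which phase 1 was drawn. The outcome being compared is defined by an intervention week that phase 1 never had.

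This is the only between-group comparison in the plan, so it is the one a reader would use to separate an effect of the app from drift over time or from being monitored. Phase 1 data collection ended in October 2019 and phase 2 recruitment began in October 2020, so the control is also non-concurrent. A p value from a test labelled control against intervention will be read as controlled evidence, which these data cannot supply in the form planned.

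**Working it through.** **The plan's own sample size.** Inputs from Sample Size and Power Calculation: SD 135.1 min, correlation 0.8, difference 30 min, 5% two-sided, 80% power.
- SD of change = 135.1 × √(2 × (1 − 0.8)) = 85.4 min.
- Exact paired t test: n = 65 gives power 0.796 and n = 66 gives 0.802, so 66. Then 66/0.95 = 69.5, so 70. The stated 66 and 70 reproduce. No sample size or power is stated for the between-phase test.

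**Overlap.** With 75 staff, 70 enrolled and R phase 1 participants still on the unit, the smallest possible overlap is max(0, R + 70 − 75).
- None left (R = 16): at least 11. If they enrol at the same rate as others, 16 × 70/75 = 14.9 expected.
- 4 left (R = 12): at least 7; 11.2 expected.
- 8 left (R = 8): at least 3; 7.5 expected.
- 11 left (R = 5): none forced; 4.7 expected.

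**Effect of overlap on the test.** Let m people be in both groups, with correlation ρ between a person's changes in the two phases. The variance of the difference is 85.4² × (1/16 + 1/66 − 2ρm/(16 × 66)); the Student t test omits the last term. Approximate true type I error at a nominal 5%:
- ρ = 0: 5%, whatever m.
- ρ = 0.3: 4.1% (m = 11) to 3.7% (m = 16).
- ρ = 0.8: 2.7% (m = 11) to 1.8% (m = 16).
- ρ = −0.3: 5.9% (m = 11) to 6.4% (m = 16).

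The documents give no value for ρ; these are assumed values showing the range.

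**Time covered by the change.**
- Phase 2: 7 + 28 = 35 days. Change runs from days 1–7 to days 29–35, which are 28 days apart.
- Pilot data: 241/14 = 17.2 days per person. With 17 days, first to last week is days 1–7 to days 11–17, which are 10 days apart.
- 14 people with 35 days each would need 490 days. From 241 days, at most 6 people could have 35 (241/35 = 6.9) and at most 8 could have 28 (241/28 = 8.6).

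**Precision as written.** Assuming the same SD of change (85.4 min) in both groups and no overlap, 16 against 66 gives SE = 85.4 × √(1/16 + 1/66) = 23.8 min and about 24% power for a 30 min difference.

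**The case against.** The case for leaving the plan alone has several sound parts.

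- A reader might infer that staff are certainly in both phases. The article never says so. A year separates the phases, the staff count is for any given time, turnover in this unit is not quantified, and phase 2 also requires a PSQI score of at least 5 and has several exclusions. Nothing is forced if 11 or more of the 16 have left, or if phase 2 enrols 59 or fewer (16 + 59 − 75 = 0). The Abstract's sentence "They will subsequently be provided with an iCBTS app for 4 weeks" could be read as the same people continuing, but it fits equally well with phase 2 participants moving from baseline to intervention.
- A reader might infer that phase 1 has no data as late as week 5. The figure of 17 days is an average. It comes from 14 people used for modelling, not the 16 with full data, and may count only the days used. Some people could have been followed for longer.
- A phase 1 change can be computed under the first-and-last-week wording, so the outcome is not impossible.
- A reader might infer that overlap inflates false positives. With positive within-person correlation the test is conservative, and with none it is unaffected.
- The Discussion already concedes that the study cannot show an effect beyond that of taking part, and the Study Overview calls the study a pilot.

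All of this stands as a limit on the wording. It does not remove the point. The article fixes the groups, the test and the significance level while leaving the control group's change undefined and people in both groups unprovided for. The concession in the Discussion addresses neither. The low power is not itself an error, because no power is claimed for this comparison; it only describes how little the test can show.

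**Conclusion.** The concern holds in a limited form. The between-phase Student t test is badly fixed for two reasons: it treats as independent two groups that very likely share people, and it probably compares changes over different elapsed times.

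The size on the document's figures is a forced overlap of at least 11 of 16 with no departures, 7 with 4 departures and none with 11 or more, and an average of about 17 days of phase 1 data against 35. The first rests on about 75 staff, 70 enrolled and an unknown turnover. The second rests on the modelling data standing for phase 1 as a whole, whose length is not stated.

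The documents do not support saying that overlap is certain, that week-4-equivalent data are absent, or that the test is anti-conservative. The point concerns this one comparison. The primary paired t test uses phase 2 alone and is unaffected, as are its 66 and 70.

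**What to change.** Replace the Student t test, and in the protocol:

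1. State how long phase 1 participants were observed and which days define their change.
2. Compare that change with the same elapsed-time window in phase 2.
3. Link people across phases with a participant key. Fit one mixed model to sleep duration from both phases, with participant effects on level and on change, or else pair the people who are in both phases. A random intercept alone would link levels and leave the correlation between a person's two changes unmodelled.
4. Add a sensitivity analysis that counts anyone in both phases in one group only, and report how many remain.
5. Report the difference with a 95% CI as an exploratory, non-concurrent comparison, without a 5% test of control against intervention.

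This needs no new data if the participant key can be made. It has two costs. First, the matched window may fall short of 4 weeks of intervention: if phase 1 ran 17 days, the matching last week in phase 2 is days 11–17, only the 4th to 10th days after the baseline week. Second, the estimate will be imprecise. With 11 shared people removed from the controls, 5 remain and the SE under the assumptions above rises to 85.4 × √(1/5 + 1/66) = 39.6 min. Removing them from phase 2 instead leaves 55 and gives 85.4 × √(1/16 + 1/55) = 24.3 min. The 24% power belongs to the Student t test as written and should not be quoted for the replacement model.

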## Results

This study was reviewed by The Clinical Research Ethics Review Committee of Mie University Hospital and was approved on January 25, 2019 (phase1) and May 17, 2020 (phase 2). Both trials are registered with the UMIN Clinical Trials Registry (phase 1: UMIN000036122, phase 2: UMIN000040547). Data collection in phase 1 was completed in October 2019, with full data obtained from 16 participants. In phase 1, the mean sleep duration was 334.68 (SD 135.1) minutes. As of September 2020, additional results from the trial were still being analyzed and evaluated. After revising and validating the optimal app function, recruitment for phase 2 started in October 2020. This study is expected to be completed by summer 2021.

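### The phase 1 versus phase 2 comparison uses a pooled-variance t test at about 16 against 66, so its 5% level depends on equal change SDs that the protocol does not support; Welch's test is a nearly free replacement

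*Protocol article*

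**What the plan says.** The section Outcome and Statistical Analysis of the protocol article defines the comparison as "Using the cases in phase 1 as the control group and the cases in phase 2 as the intervention group". It then says that "the means and SDs of the change in sleep duration will be calculated, and the Student *t* test will be performed", and sets the level at "at a significance level of 5% on both sides. Additionally, descriptive analysis will be performed". It names no unequal-variance form and no check of the variances.

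The group sizes come from two other places. The Results section reports: "Data collection in phase 1 was completed in October 2019, with full data obtained from 16 participants". Sample Size and Power Calculation gives the phase 2 target: the number needed for the primary paired "test was calculated to be 66", raised to 70 enrolled for about 5% dropout. No sample size, power or change SD is stated for the between-phase comparison.

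**The concern.** In its usual meaning the Student two-sample t test pools the two variances. With equal group sizes that does little harm when the SDs differ. With one group about four times the other, the pooled SD is set almost entirely by the larger group, while the uncertainty of the difference comes mostly from the smaller one. A difference in SD then passes into the error rate.

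Nothing in the article supports equal SDs of change. The stated similarity between phases concerns mean baseline sleep. The assumption of an unchanged SD concerns the level of sleep at week 4 within phase 2. Neither is a statement about the SD of change across phases.

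This is the only between-group test in the plan and the only one that bears on change without the app, so its p value is likely to be read with interest even though it is not primary.

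**Working it through.** **Inputs from the article.** Phase 1 n = 16. Phase 2 n = 66 evaluable, 70 enrolled. Sleep SD 135.1 min, within-person correlation 0.8 and primary effect 30 min (Sample Size and Power Calculation). Two-sided 5%.

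**The plan's own figure first.** Change SD = 135.1 × √(2 × (1 − 0.8)) = 85.4 min. A paired t test for 30 min, using the noncentral t distribution, has 79.6% power at n = 65 and 80.2% at n = 66. The stated 66 reproduces, and 66 / 0.95 = 69.5 gives 70.

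**Why the imbalance matters.** Let k be the phase 1/phase 2 ratio of change SDs, with the phase 2 SD set to 1.

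- Variance that the Student test uses, on average: [(15k² + 65) / 80] × (1/16 + 1/66)
- True variance of the difference: k²/16 + 1/66

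At k = 1.5 the first is 1.234 × 0.07765 = 0.0959 and the second is 0.1406 + 0.0152 = 0.1558. The standard error used is √(0.0959 / 0.1558) = 0.784 of the true one. The cut-off of 1.990 (80 df) therefore acts like 1.990 × 0.784 = 1.56, a two-sided tail of about 12%.

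At k = 0.5 the two variances are 0.859 × 0.07765 = 0.0667 and 0.0156 + 0.0152 = 0.0308. The ratio of standard errors is 1.47, the effective cut-off is 2.93, and the tail is about 0.3%.

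**Simulated type I error at nominal 5%, normal data, 16 against 66.** The ratios are an assumed range, because the article gives none.

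| Phase 1 / phase 2 change SD | Student | Welch |
|---|---|---|
| 0.5 | about 0.5% | 5.0% |
| 0.67 | 1.4% | 5.0% |
| 0.9 | 3.7% | 5.1% |
| 1.0 | 5.0% | 5.1% |
| 1.1 | 6.4% | 5.1% |
| 1.25 | 8.7% | 5.1% |
| 1.5 | 12.3% | 5.0% |
| 2.0 | 18.4% | 5.0% |

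Repeat runs agree to about 0.1 point. With 70 in phase 2 the Student range is 0.4% to 18.9%. With 66 in each group the Student test stays at 5.0% to 5.1% over the same ratios, so the imbalance is the cause.

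**On the scale of the article's SD.** Keep correlation 0.8 in phase 2 (change SD 85.4). An assumed correlation of 0.7 in phase 1 gives a change SD of 135.1 × √0.6 = 104.6 and a Student error of 8.3%. An assumed 0.9 gives 135.1 × √0.2 = 60.4 and 1.7%.

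**Price of Welch when the SDs are equal (85.4 min).** The standard error is 85.4 × √(1/16 + 1/66) = 23.8 min. Power for a 30-minute difference is 23.8% with Student and 22.7% with Welch.

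**The case against.** A reader might infer from the upper half of the table that this comparison will produce false positives. The article does not support that. Those figures need phase 1 to vary more than phase 2, and nothing points that way. The one mechanism that the design suggests is differing individual response to the app, which occurs only in phase 2. That would make the larger group the more variable one and the Student test conservative, with lost power as the price.

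A reader might also infer unequal SDs from the length of observation. The model-building data are "a total of 241 days of data collection" from 14 people, 241 / 14 = 17.2 days each, against 5 weeks (35 days) in phase 2. This does not carry over. Those 14 are a modelling data set, whereas the controls here are the 16 with full data, and the article does not state how long phase 1 followed them.

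The remaining objections concern weight, and they stand. For ratios within about 10% of 1 the distortion is small. The study is described as a pilot, the comparison is additional to a paired primary analysis, and its power for 30 minutes is only about 24%. The Discussion already concedes that the study cannot separate the effect of iCBTS from that of taking part. The control group is also non-randomised and earlier: phase 1 data were complete in October 2019, and phase 2 recruitment began in October 2020. Both phases draw on one unit of about 75 staff, so some people may appear in both; the article does not say. No choice of t test repairs these weaknesses.

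None of this justifies the equal-variance assumption. It only limits how much turns on it.

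**Conclusion.** The point holds as a minor refinement. The article fixes a test whose 5% level rests on an unsupported equality of change SDs, at an allocation where that equality matters. The miscalibration is conditional: none at equal SDs, and otherwise in a direction that the article does not let one determine. The error figures rest on normally distributed changes, independent groups of 16 and 66, the assumed SD ratios, and the usual equal-variance meaning of the Student t test. The primary paired t test and its sample size are not touched.

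**What to change.** In Outcome and Statistical Analysis, replace the Student t test for the phase 1 versus phase 2 comparison with Welch's unequal-variance t test, and report the difference in mean change with its Welch 95% CI. Keep the two-sided 5% level.

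The cost is a few words, no extra data, and about 1 point of power at 30 minutes if the SDs prove equal. The result should still be presented as a comparison with a non-randomised, earlier control, because the change of test does not alter that.

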## Results

This study was reviewed by The Clinical Research Ethics Review Committee of Mie University Hospital and was approved on January 25, 2019 (phase1) and May 17, 2020 (phase 2). Both trials are registered with the UMIN Clinical Trials Registry (phase 1: UMIN000036122, phase 2: UMIN000040547). Data collection in phase 1 was completed in October 2019, with full data obtained from 16 participants. In phase 1, the mean sleep duration was 334.68 (SD 135.1) minutes. As of September 2020, additional results from the trial were still being analyzed and evaluated. After revising and validating the optimal app function, recruitment for phase 2 started in October 2020. This study is expected to be completed by summer 2021.

